## Abstract

**Background:**

An increasing number of Canadians are living beyond cancer, with many individuals experiencing long-lasting side effects of cancer and its treatments. Research shows that engaging in rehabilitation during and after cancer treatment can reduce side effects and improve quality of life. However, less than 30% of individuals with cancer have access to rehabilitation services. The purpose of this pilot trial is to assess the feasibility of a novel PT Navigator role in an acute cancer care setting for individuals undergoing treatment for cancer.

**Methods:**

*Study Design:* Pilot randomized controlled trial. *Eligibility:* Adults aged ≥18 years who are currently undergoing cancer treatment for any type of cancer. *Intervention:* The intervention group includes six consultative sessions by a PT Navigator over a maximum of eighteen weeks. *Randomization:* Participants will be randomly allocated using a 1:1 allocation ratio to receive the intervention with the PT Navigator or usual care. *Outcomes:* The primary feasibility outcome is adherence rate. Secondary outcomes include recruitment rate, retention rate, satisfaction and preliminary effectiveness, including health-related quality of life, self-reported exercise volume, health care utilization, activity limitation, functional strength, exercise capacity, and overall impairment score. *Analysis:* Outcomes will be assessed at baseline, post-intervention, and two month follow up. Feasibility and preliminary effectiveness will be assessed using descriptive statistics.

**Discussion:**

This study aims to assess the feasibility of a novel PT Navigator role in an acute cancer care setting in Ontario, Canada. This pilot trial will evaluate process and resource capabilities before testing the role within a larger scale randomized controlled trial. The overall project goal is to facilitate regular assessment by a rehabilitation professional to promote early identification of physical impairment and early intervention to manage impairment as a standard component of cancer care in Canada.

**Trial registration:**

ClinicalTrials.gov ID NCT07045740.

## Introduction

The burden of cancer in Canada is growing with nearly one in two [1], or 43% [2], of Canadians being diagnosed with cancer throughout their lifetime. With survival rates increasing [2,3], individuals living beyond cancer face many persistent symptoms that can affect their day-to-day functioning and overall quality of life [4–6]. Cancer and cancer treatments can lead to significant adverse effects such as pain, fatigue, lymphedema and reduced mobility. Research demonstrates that engaging in physical activity and rehabilitation can enhance quality of life, improve physical function, and reduce anxiety and depression amongst those living with and beyond cancer [7,8]. Additionally, recently published research involving patients with colorectal cancer has shown that engaging in physical activity and exercise during and after cancer treatment reduced the risk of cancer recurrence and resulted in improved overall survival [9]. Physiotherapists (PTs) are specialists in physical rehabilitation and health promotion in Canada [10]. Current provincial [11] and international [12,13] oncology clinical practice guidelines recommend that PTs are included as part of the cancer care team across all stages of cancer treatment. However, only 30% of cancer survivors in Canada have access to rehabilitation [14] leaving individuals to find and fund their own rehabilitation, something many are unable to do [15,16].

There is a need to identify gaps in service and challenges to accessing care when considering rehabilitation for managing long-term impairments [17]. In 2012, Stout et al. developed a Prospective Surveillance Model (PSM) for rehabilitation for women with breast cancer [18]. The goal of the PSM is to facilitate early identification of impairments through ongoing surveillance throughout all stages of cancer care [18]. Current literature examining the application of the PSM across several countries has demonstrated cost-effectiveness [19–21] and provided evidence that proactive monitoring and early intervention can prevent side effects [20,22,23]. In addition to the PSM, healthcare navigator roles have been shown to reduce barriers to accessing treatment [17,24], enhance care processes [17,24], and reduce clinical costs across healthcare settings [24,25].

Canadians living with cancer have expressed an unmet need and want to participate in physical activity, exercise, and rehabilitation to alleviate long term side effects of cancer, facilitate their return to work, and increase quality of life [26–28]. Navigators frequently collaborate with patients and their families to provide knowledge, support, and guidance on local health care systems or community services available to them [29]. A scoping review exploring PTs in a navigator role found that navigation in cancer treatment settings has increasingly emerged over the last ten years, however, currently most navigator positions in cancer care settings are held by nurses and nearly all PT Navigator roles are from the United States of America [30]. The review further highlighted how a PT Navigator could effectively identify and address common patient reported barriers and facilitate awareness on the benefits of rehabilitation across the cancer care continuum [30]. Moreover, the role would allow symptom assessment and early management to be a part of standard and routine care [16,30]. Despite the known benefits of implementing prospective monitoring and patient navigation, no study evaluating the use of a PT Navigator has been conducted in Canada.

## Methods

### Study purpose

The purpose of this pilot RCT is to examine the feasibility of a PT Navigator role for individuals living with cancer receiving cancer treatment in an acute cancer care setting. Specifically, our research questions are as follows:

*Research question 1 (Primary):* Is a PT-Navigator role feasible, as measured by adherence, recruitment, retention, and satisfaction rates, to implement at a cancer institution in Ontario, Canada?

*Research question 2 (Secondary):* Do individuals with cancer who are monitored by a PT-Navigator demonstrate trends for improved outcomes in overall impairment score, health-related quality of life, physical activity levels, exercise capacity, functional strength, activity limitation, and a reduction in health care utilization costs compared to individuals with cancer who are not monitored by a PT Navigator during treatment?

### Study design

This is a two-arm pilot randomized controlled trial [31] (Figs 1 and 2). This protocol is reported according to the CONSORT guidelines extended to pilot and feasibility trials [32] and the SPIRIT guidelines for protocols of randomized trials [33]. See S1 Appendix for the SPIRIT 2025 checklist of items to address in a randomized trial protocol. The Hamilton Integrated Research Ethics Board has reviewed and approved this study (#18583). The PT Navigator role was developed and examined first using a scoping review [30] to explore the current design and utility of a PT in a navigational role and further developed to a Canadian context using a modified Delphi study [34] seeking the feedback of a role proposal through various end-users across Canada (e.g., PTs, oncologists, nurses). See S2 Appendix for the finalized role description.

**Fig 1 pone.0351761.g001:**
[figure not shown]
Study Flow Chart.

**Fig 2 pone.0351761.g002:**
[figure not shown]
Schedule of Enrollment, Interventions, and Assessments (SPIRIT Statement).

### Recruitment

All eligible individuals living with cancer who attend the Juravinski Cancer Centre (JCC), a regional cancer care centre in Hamilton, Ontario, between November 2025 and February 2026, will be approached consecutively by their medical oncologist to participate in the study. The medical oncologists will connect the potential participant to the research team (HE) who will confirm eligibility and start the consent process prior to enrollment. Consent will be obtained both verbally and using written documentation through ethics-approved consent forms, further witnessed by a member of the research team (HE). There will also be the opportunity for self-referral as recruitment flyers will be advertised within the cancer centre for patients to contact the study team directly. A rolling recruitment and enrollment strategy will be used until the required sample size is achieved. Participants allocated to the intervention group will be introduced by their medical oncologist to the PT Navigator early during their cancer treatment (i.e., within the first month).

### Participants

Eligible participants will include adults aged ≥18 years old, who have been recently diagnosed with any type/stage of cancer who are/will be receiving cancer treatment (e.g., chemotherapy, radiation, immunotherapy), are English-speaking, and are community-dwelling. Participants will be excluded from the study if they have a self-reported physical or cognitive impairment that would prevent them from carrying out a physical assessment.

### Sample size

Our sample size was calculated using a confidence interval approach based on recommendations for pilot trials [35–37]. Specifically, we used a 95% confidence interval, a desired margin of error of 0.2, and our estimated 70% adherence rate to determine feasibility. The calculated sample size was 20 participants. However, to account for a 20% dropout rate, the final sample size will include 13 participants per group (26 total). It is important to consider that as the pilot study is exploratory in nature, this sample size is not powered to detect meaningful change between groups.

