The PT Navigator will also assist participants in setting goals and developing action plans focused on functional activity or reduction in symptoms during each visit. Importantly, the PT Navigator will serve as an advocate to ensure the patient feels supported and aware of all resources available to them. The participants allocated to the intervention group will also be given the PT Navigator’s contact information and will be encouraged to communicate with them if they ever have any questions or concerns throughout the intervention period.

Control (Usual Care). Participants in this group will have no interaction with the PT Navigator. They will continue with usual care regarding rehabilitation from their medical oncologist and oncology care team. This ranges from no discussion of rehabilitation to general advice to stay physically active [41]. We will track any interventions received outside of the hospital by all participants (e.g., visits with family doctor, community PT) using the health care utilization questionnaire included as a study outcome.

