** *Adherence* **			
Proportion of sessions attended with the PT Navigator	>70% of sessions with the PT Navigator were attended by the participants	50-70% of sessions with the PT Navigator were attended by the participants	<50% of sessions with the PT Navigator were attended by the participants

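### The ±0.2 margin for adherence is calculated on participants from both arms, but adherence can be observed only in the 13 intervention participants, so the stated precision is unsupported

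*Protocol article*

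**What the plan says.** The Sample size section rests on one precision calculation: "we used a 95% confidence interval, a desired margin of error of 0.2, and our estimated 70% adherence rate to determine feasibility". It reports that "The calculated sample size was 20 participants" and then, "to account for a 20% dropout rate", that "the final sample size will include 13 participants per group (26 total").

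The Outcomes and Feasibility sections make adherence the primary feasibility outcome. Table 2 defines it as "Proportion of sessions attended with the PT Navigator", with green above 70%, yellow from 50% to 70% and red below 50%. The Procedure section plans six sessions for each intervention participant. Of the usual-care arm it says: "Participants in this group will have no interaction with the PT Navigator".

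**The concern.** The calculation treats all participants as one sample in which adherence is measured. By the protocol's own definition, adherence has no meaning in the control arm, so half of the 26 add nothing to the estimate that the number was chosen to make precise.

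There is also a mismatch of unit. The formula treats adherence as one yes/no result per participant, while Table 2 takes a proportion of sessions, up to six of them clustered in each participant.

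This is the only justification given for the sample size, and it concerns the primary outcome. A reader would expect adherence to be known to within 20 percentage points when it is read against the traffic-light limits, and might carry that figure into planning the larger trial.

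**Working it through.** **Inputs.** From the Sample size section: 95% confidence (taken as two-sided, z = 1.96), margin d = 0.20, adherence p = 0.70, dropout 20%, and 13 per group. From the Procedure section: six sessions per intervention participant. The within-participant correlation of attendance (ICC) is not given, so a range is assumed.

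**1. Reproduce the plan's figure.** n = z²p(1 − p)/d² = 1.96² × 0.70 × 0.30 / 0.20² = 20.17, which matches the stated 20 when rounded to the nearest whole number. For dropout, 20/0.8 = 25, made even for 1:1 allocation = 26. Both figures reproduce, but only as a single sample in which every participant has an adherence result.

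**2. Apply the same formula to those who can contribute.** Half-width = 1.96 × √(0.21/n):

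| Participants contributing to adherence | Half-width | Interval around 70% |
|---|---|---|
| 20 (the plan's calculation) | ±0.201 | 50% to 90% |
| 13 (intervention arm) | ±0.249 | 45% to 95% |
| 10 (13 × 0.8 = 10.4, if dropouts are not evaluable) | ±0.284 | 42% to 98% |

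Wilson intervals, which behave better at this size, are 42% to 87% for 9/13 and 40% to 89% for 7/10. At ±0.20 the lower limit sits on the 50% red-light boundary. With 13 participants it lies inside the red zone.

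**3. Use the outcome as Table 2 defines it.** There are 13 × 6 = 78 planned sessions. With six sessions per participant, the effective number is 78/(1 + 5 × ICC), and the half-width is 1.96 × √(0.21/effective number):

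| Assumed ICC | Effective number | Half-width |
|---|---|---|
| 0 | 78.0 | ±0.10 |
| 0.3 | 31.2 | ±0.16 |
| 0.5 | 22.3 | ±0.19 |
| 1 | 13.0 | ±0.25 |

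Setting the half-width to 0.20 and solving gives ICC = [(0.20/1.96)² × 78/0.21 − 1]/5 ≈ 0.57. With 13 participants, ±0.2 is met at or below that value. With 10 participants (60 sessions) the limit is about 0.40. The participant-level ±0.25 is the ICC = 1 case, in which each participant attends every session or none.

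**4. Size needed to keep ±0.2 on the participant basis.** The intervention arm would need 20 to 21 evaluable participants. After 20% dropout that is 20/0.8 = 25 to 21/0.8 = 26.25, rounded up to 27, or 50 to 54 in total at 1:1.

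**The case against.** The strongest reply is that Table 2 counts sessions, so 13 participants with six sessions each may well give ±0.2 or better. That stands: nothing in the protocol excludes an ICC below 0.57. It does not rescue the calculation, which counts participants and states no ICC. A reader might infer that the margin is missed; the documents support only that it has not been justified.

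A second reply is that this is an exploratory pilot and that the traffic light uses the observed percentage, with no rule tied to the interval. This is fair, and it limits the consequence. Even the intended 50% to 90% spans yellow and green, so the error does not create that ambiguity; it only moves the lower limit into red. The disclaimer in the Sample size section, however, covers power to detect differences between groups, not the precision of adherence.

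Two further inferences are tempting and should not be drawn:

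- **Dropouts are excluded from adherence.** Inflating for dropout may suggest this, but the section only raises the number, and Table 2 excludes nobody. The ±0.28 is therefore conditional on 10 evaluable participants, not a statement of what the plan will do.
- **The ±0.2 really belongs to retention, which uses both arms.** The protocol attaches the margin to adherence alone. At the 80% retention implied by 20% dropout, the half-width with 26 would be 1.96 × √(0.16/26) ≈ ±0.15, a different figure.

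**Conclusion.** The sample-size statement is wrong as written. A number derived for one sample is spread over two arms, although the outcome exists in only one of them. On the protocol's own formula, with p = 0.70 and a normal approximation, the half-width is ±0.25 with 13 participants (±0.28 with 10) instead of ±0.20.

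For the session proportion in Table 2, the half-width lies between about ±0.10 and ±0.25 with 13 participants, depending on an ICC that is not stated. The ±0.25 is thus a conservative upper case and not the expected value. The 26 participants, the thresholds and the design can stay; what needs correction is the claimed precision of the primary outcome.

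**What to change.** Keep 26 participants and make two changes.

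1. In the Sample size section, say that adherence is estimated in the 13 intervention participants. Then either give a 95% half-width of up to about ±0.25 at 70% adherence, labelled as the conservative participant-level case, or redo the figure at session level with a stated ICC and the reason for choosing it.
2. In the Analysis section, which already plans 95% confidence intervals, say that the interval for adherence takes the participant as the unit, because sessions are clustered within participants.

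The cost is a change of wording and one analysis line, with no extra participants. The downside is that the stated margin becomes less favourable if the conservative figure is used.

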### Randomization and allocation

Randomization will be completed by a member of the research team using RedCap [38]. The 1:1 randomization schedule will be generated using permuted blocks by a member of the research team not involved in recruitment, randomization or treatment delivery. Participants allocated to the intervention group will receive a phone call by the PT Navigator to schedule the first intervention session.

### Blinding

Due to the nature of the intervention, the participants and PT Navigator cannot be blinded to group allocation. All data will be de-identified for data analysis by a blinded statistician.

### Procedure

Intervention Group (PT Navigator). The interactions with the PT Navigator will occur at the JCC. The PT Navigator will follow the PSM [18] for ongoing monitoring and surveillance. The PT Navigator will check-in with participants approximately every two to three weeks over a maximum of 18 weeks (i.e., six sessions total with the PT Navigator) when they are already coming to the JCC for another appointment. Interactions with the PT Navigator will be 30 minutes (follow-ups) to one hour (initial assessment). Fig 3 represents the PT Navigator interaction process.

**Fig 3 pone.0351761.g003:**
[figure not shown]
PT Navigator Role Process.

The PT Navigator will administer outcome measures and continuously screen for complications or side effects of treatment (i.e., fatigue, chemotherapy-induced peripheral neuropathy). See Table 1 for a summary of outcome measures and scoring interpretations to guide the PT Navigator in their decision-making on next steps. However, the PT Navigator will always use their clinical reasoning to determine what clinical tests they will assess and to guide their decision making. The PT Navigator will triage participants with one or more of the following steps based on their assessment: 1) Develop a rehabilitation plan (i.e., discuss self-management strategies, exercise prescription, goal setting, rehabilitation barrier identification), 2) Refer the individual to a community program (i.e., the patient needs more frequent follow-up and/or more supervision with rehabilitation services), 3) Refer to another health care discipline (i.e., the patient needs care outside of the PT scope of practice – for example, to discuss changes in weight and appetite with a dietician), 4) Continue with ongoing surveillance (i.e., no complications of treatment identified – continue to provide positive reassurance, answer questions, and provide education on maintenance strategies). Note, patient consent will be received throughout all interactions and triaging decisions with the PT Navigator, including regarding any communication and documentation which will follow the Documentation Standard as set out by the College of Physiotherapists of Ontario [39] and the Personal Health Information Protection Act [40].

**Table 1 pone.0351761.t001:** Outcome Measures and Decision-Making Process.

Outcome(s) Assessed and Measure Used	Scoring Interpretation	Decision-Making Process
**Overall Impairment** Edmonton Symptom Assessment Scale (ESAS)	0 = none 1–3 = mild 4–6 = moderate 7–10 = severe -symptoms are assessed on a 0–10 scale with 10 representing worst severity -minimal clinically important difference = 2 points	-**mild** = PT Navigator to provide education on monitoring and how to prevent symptom worsening -**moderate/severe** = PT Navigator continues monitoring, communicate symptoms with medical team, and prescribe/deliver intervention or referral as appropriate
**Self-Reported Exercise Volume** Godin Leisure-Time Questionnaire	24 units or more = active 14-23 units = moderately active less than 14 units = insufficiently active/sedentary -minimal clinically important difference = 10% change in physical activity from baseline	-**active** = PT Navigator provides support and encouragement -**moderately active** = PT Navigator provides physical activity education and goal setting -**sedentary** = PT Navigator identifies barriers with patient, goal setting, and prescribe/deliver exercise intervention
**Health-Related Quality of Life** Functional Assessment of Cancer Therapy – General (Fact-G)	Total score: 0–108 -physical (0–28) -social (0–28) -emotional (0–24) -functional (0–28) -items are assessed from 0 to 4 with higher scores indicating better perceived QOL -minimal clinically important difference = 4–7 points	-**total score >90** = PT Navigator continues monitoring and providing support and education where appropriate -**total score 50–89** = PT Navigator continues monitoring, communicate concerns with medical team, and prescribe/deliver intervention or referral as appropriate -**total score <49** = PT Navigator informs medical team immediately for follow up, prescribe/deliver intervention or referral as appropriate
**Activity Limitation** Patient-Specific Functional Scale (PSFS)	- score of 0 indicates the activity cannot be performed, while a score of 10 indicates the activity can be performed at the same level as before their problem -minimal clinically important difference not established in cancer	-a **decrease in 2 points** in an activity score – the PT Navigator to prescribe/deliver an exercise intervention or refer to community physiotherapy as appropriate (i.e., the patient needs frequent follow up)
**Range of Motion** **Muscle Strength** Goniometry and Grip Strength (Dynamometer)	-range of motion normative values vary per joint being examined -to compare grip strength to normative values of the general population and if applicable, normative values of patients with advanced cancer -minimal clinically important difference not established in cancer	-a **decrease of 10 degrees** in range of motion and/or if grip strength is **less than the normative value** for the patient’s age group and/or **there is a reduction of 5 kg since baseline** – the PT Navigator to prescribe/deliver an exercise intervention or refer to community physiotherapy as appropriate (i.e., the patient needs frequent follow up)
**Functional Lower Extremity Strength** 30-Second Sit to Stand	-to compare total repetitions completed to normative values of the general population with respect to patient’s age group -minimal clinically important difference not established in cancer	-if score is **less than the normative value** for the patient’s age group and/or there is a **decrease in 2 repetitions since baseline** – the PT Navigator will prescribe/deliver an exercise intervention or refer to community physiotherapy as appropriate (i.e., the patient needs frequent follow up)
**Mobility** Timed Up and Go	-to compare time to normative values of the general population with respect to patient’s age group -minimal clinically important difference not established in cancer	-if score is **less than the normative value** for the patient’s age group and/or there is **an increase in 3 seconds since baseline** – the PT Navigator will prescribe/deliver an exercise intervention or refer to community physiotherapy as appropriate (i.e., the patient needs frequent follow up)
**Aerobic Capacity** 6-Minute Walk Test	-to compare distance walked to normative values of the general population with respect to patient’s age group -minimal clinically important difference = 22–66 metres	-if walked distance is **less than the normative value** for the patient’s age group and/or there is a **decrease in 42 metres since baseline** – the PT Navigator will prescribe/deliver an exercise intervention or refer to community physiotherapy as appropriate (i.e., the patient needs frequent follow up)

*Minimal clinically important difference (MCID) is the minimum difference that the patient can recognize as beneficial.

**Note: this table serves as a reference guide. The PT Navigator can administer other outcome measures as appropriate and will always follow their clinical training and reasoning when considering decision-making. References to support scoring interpretation and triaging decisions can be found in the finalized role description found in S2 Appendix.

The PT Navigator will also assist participants in setting goals and developing action plans focused on functional activity or reduction in symptoms during each visit. Importantly, the PT Navigator will serve as an advocate to ensure the patient feels supported and aware of all resources available to them. The participants allocated to the intervention group will also be given the PT Navigator’s contact information and will be encouraged to communicate with them if they ever have any questions or concerns throughout the intervention period.

Control (Usual Care). Participants in this group will have no interaction with the PT Navigator. They will continue with usual care regarding rehabilitation from their medical oncologist and oncology care team. This ranges from no discussion of rehabilitation to general advice to stay physically active [41]. We will track any interventions received outside of the hospital by all participants (e.g., visits with family doctor, community PT) using the health care utilization questionnaire included as a study outcome.

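### The norm-based Timed Up and Go trigger in Table 1 runs the wrong way: it prompts action for faster-than-norm participants and none for stable slow ones

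*Protocol article*

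**What the plan says.** Table 1 of the protocol article (Methods, Procedure) links each measure to a scoring interpretation and a next step for the PT Navigator.

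- **Timed Up and Go, scoring column:** the instruction is "to compare time to normative values of the general population with respect to patient’s age group". The score is therefore a time.
- **Timed Up and Go, decision column:** two triggers joined by and/or lead to the same action, an exercise intervention or referral to community physiotherapy. One fires when the score is "less than the normative value" for the age group. The other fires on "an increase in 3 seconds since baseline".
- **Status of the table:** its footnote says "this table serves as a reference guide". The Procedure text says "the PT Navigator will always use their clinical reasoning to determine what clinical tests they will assess".
- **FACT-G row:** the top band is "total score >90", the middle band runs from 50 to 89, and the bottom band is "total score <49".

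**The concern.** On a timed test a longer time is worse, and the 3-second change trigger shows that the authors intend this. The norm trigger in the same cell nevertheless fires on a shorter time. Read literally, it sends participants who move faster than their age norm to exercise or physiotherapy. It gives no prompt for a participant who is slower than the norm but has not slowed by a further 3 seconds.

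This matters most at a participant's first assessment. If that measurement is the baseline, there is no change to act on, so the norm trigger is the only part of the row that can fire. The stated goal of the project is early identification of impairment, and the pilot is meant to settle procedures before a larger trial. What is at stake is how the intervention is delivered, not how the trial is analysed.

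**Working it through.** The article gives no figure to reproduce here. The check is on the logic of the written rule.

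**1. Direction of the norm-based triggers in Table 1**

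| Measure | Worse direction | Norm trigger | Change trigger | Consistent? |
|---|---|---|---|---|
| Grip strength | lower | below norm | fall of 5 kg | yes |
| 30-second sit to stand | lower | below norm | fall of 2 repetitions | yes |
| 6-minute walk | lower | below norm | fall of 42 m | yes |
| Timed Up and Go | higher (time) | below norm | rise of 3 s | **no** |

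One of four norm triggers is reversed. In the Timed Up and Go row the change trigger was adapted to a lower-is-better test and the norm trigger was not. Wording carried over from the neighbouring rows is the likely cause.

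**2. The rule applied to example participants**

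The article gives no norm, so 10 s is assumed for illustration. Times are baseline, then current. The change trigger is taken as a rise of at least 3 s.

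- As written: act if current < 10 or current − baseline ≥ 3.
- Corrected: act if current > 10 or current − baseline ≥ 3.

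| Baseline, current (s) | Rise (s) | As written | Corrected |
|---|---|---|---|
| 7, 7 | 0 | act | no action |
| 12, 12 | 0 | no action | act |
| 14, 16 | 2 | no action | act |
| 12, 15 | 3 | act (change only) | act |

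An assumed norm of 9 s gives the same pattern: 7 s stable prompts action, while 14 s stable and 12 s rising to 14 s do not. The direction of the error does not depend on the norm chosen.

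**3. How many assessments could be affected**

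The intervention arm has 13 participants with up to six sessions each, so with one test per session the ceiling is 13 × 6 = 78 assessments. The floor is 0, because the PT Navigator chooses which tests to use. The article does not allow a narrower range.

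**4. FACT-G bands (a separate and lesser point)**

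The total runs from 0 to 108, which is 109 whole-number values.

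- Above 90: 91 to 108, 18 values.
- Middle band: 50 to 89, 40 values.
- Below 49: 0 to 48, 49 values.

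18 + 40 + 49 = 107, so two totals, 49 and 90, fall in no band. On either side of 49 the actions are similar: both involve the medical team and intervention or referral, and the lower band adds urgency. On either side of 90 they differ more: monitoring, support and education above, and contact with the medical team with intervention or referral below. This is a gap, not a contradiction.

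**The case against.** The strongest reply is that nobody will be misled. The user is a registered physiotherapist with extensive training, the correct direction is evident from the next clause of the same cell, the actions are to be taken as appropriate, and both the Procedure text and the table footnote put clinical reasoning above the table. No participant is triaged automatically. Slow participants may also be picked up by the sit-to-stand and 6-minute walk rows, which point the right way. Timed Up and Go is not among the trial outcomes, and adherence counts sessions attended, not triage decisions.

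All of this stands, and it keeps the point minor. It does not make the cell correct: relying on the clinician to override a line concedes that the line is wrong. Reading *less than* loosely as *worse than* does not work either, because the adjacent column defines the score as a time and the same phrase is meant numerically in the other three rows.

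Two further limits are fair. S2 Appendix, which holds the finalized role description, is not available here, so the error is established only for the article's table. The FACT-G gap is a different kind of slip, and a clinician would settle 49 or 90 by judgement; it is mentioned only because it can be closed in the same edit.

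**Conclusion.** The concern holds, as a minor error. The norm-based Timed Up and Go trigger is reversed as written and contradicts the change trigger beside it. This rests only on the text of the row; the 10 s and 9 s norms are illustrations. The number of assessments touched is unknown, anywhere from 0 to 78. Sample size, the primary adherence outcome, the other feasibility criteria and the effectiveness analyses do not depend on it. The effect is confined to the guidance given to the PT Navigator, and clinical judgement will probably absorb most of it.

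**What to change.** - In the Timed Up and Go decision cell, change *less* to *greater* in the norm trigger, so that a time slower than the age norm prompts action.
- Close the FACT-G bands, for example as ≥90, 50–89 and ≤49, which assigns each of the 109 totals to exactly one band. That example puts 90 in the lighter-action band; the investigators should confirm that they want this, or use >90 and 50–90 instead.
- Check whether S2 Appendix repeats either slip, and correct it there if so.
- Recruitment began in November 2025, so send the PT Navigator a short note now.

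The cost is one word in one cell, the boundary values in another, one check and one message. Design, sample size and analysis stay as they are.
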